**Fig. 2 Fig2:**
[figure not shown]
Structure of sessions (experimental group)

To perform the exercise, a series of guidelines and progressions will be followed, which are described in the Additional file 1. The physiotherapists that will apply this PE protocol in the participating PC centres, will receive training on how to perform the program, what to say to patients, and how to resolve conflicts that may arise during the development of the program.

#### Control group intervention

The control group will receive the standard care treatment carried out in the PC physiotherapy units that is supported by the current physiotherapy protocols in primary care of Castilla y León [58]. The treatment consists of 15 sessions of thermotherapy and analgesic electrotherapy in the area of pain, and the guidelines for the exercises recommended by the SERMEF (Spanish Society of Physic Medicine and Rehabilitation) [59].

### Sample size calculation

A total of 63 individuals by each group of treatment will allow detecting, in numerical variables, differences between pairs of group mean in a magnitude corresponding to 50% of the standard deviation (an effect size of 50%) with a probability of 80%, keeping the type I error at a 5% level. By taking into account an attrition rate of 25%, it would be necessary to include 78 individuals in each group. The calculation has been done using G*Power 3.1.

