## Methods and study design

The clinical trial has been registered (Clinicaltrials.gov NCT03654235) and has received approval from the Ethics Committee of Clinical Investigation (CEIC) of the East Valladolid health area (CASVE-NM _ 16–252) and of the CEIC of the West Valladolid health area (CEIC: 26/17).

This study protocol describes the design of a multicentric randomised clinical trial (RCT) of parallel groups (ratio 1:1) to be carried out in 10 health centres within the Public Health network areas of East Valladolid and West Valladolid, belonging to the public health service of Castilla y León (Spain). The study protocol conforms with the standard protocol items: Recommendations for Interventional Trials (SPIRIT) [48] while the RCT conforms to the Consolidated Standards of Reporting Trials (CONSORT) [49].

Patients will be recruited from family medicine consultations and will be referred to PC physiotherapy units. For patient recruitment, the questionnaire contained in Annex I are used. The RCT flow diagram is shown in Annex I.

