### Statistical analysis

Numerical variables will be summarised with means and standard deviations and categorical ones with percentages. Those numerical variables showing a distribution very far from the normal one will be transformed for getting resulting distributions close to the normal one, or in the opposite case, they will be summarised by using percentiles. For the graphical representation of the numerical variables’ distribution in each treatment group, we will use box and whisker plots. For representing categorical variables, pie charts will be used. In order to test the equality of means for numerical variables, we will apply the Student’s t, if the corresponding distributions are not far from the normal one. In the opposite scenario, we will calculate the Wilcoxon–Mann–Whitney statistics. For testing the association between qualitative variables, we will use Chi-squared statistics, if it is allowed by the observed frequencies in the associated joint distribution. On the contrary, we will re-categorise these variables for reducing them to dichotomous ones, if necessary, and will apply the Fisher exact test. As a function of the observed response to the treatment in numerical variables or the observed change in them, we will build several definitions of success/failure for the result of treatment in individuals. We will fit logistic regression models for predicting the success of the treatment by using the previously mentioned definitions. In these models, those variables which show a statistically significant relationship with the corresponding response variables in the univariate analysis and the variable selection procedures will be included. These models will provide us, as a by-product, odds ratio values for estimating the comparative risk of success associated with each explanatory variable corrected by the presence of the other variables included in them. We will obtain estimates for the sensitivity/specificity of predictive rules derived from these models. It will be considered as statistically significant *p*-values lower than 0.05. Data analysis will be carried by using the R statistical software.

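### The sample size figures do not agree: 78 per group with 25% attrition leaves about 58 completers, not 63, and power of about 76% rather than 80%

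*Protocol article*

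**What the plan says.** The section Sample size calculation is the only place in the protocol article that gives a sample size or an attrition rate. It opens with the evaluable number: "A total of 63 individuals by each group of treatment will allow detecting, in numerical variables, differences between pairs of group mean". The target difference is given as "in a magnitude corresponding to 50% of the standard deviation (an effect size of 50"%), that is, d = 0.5. Power is stated as "with a probability of 80"% and the error rate as "keeping the type I error at a 5% level". Whether the test is one-sided or two-sided is not said. The section credits the calculation to G*Power 3.1.

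The allowance for losses follows: "By taking into account an attrition rate of 25%, it would be necessary to include 78 individuals in each group". No inflation formula is printed, and no visit is attached to the 25%.

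Two other sections supply inputs. Methods and study design describes a "multicentric randomised clinical trial (RCT) of parallel groups (ratio 1:1"). Statistical analysis names the test: "In order to test the equality of means for numerical variables, we will apply the Student’s t", with a rank test as the alternative when the distribution is far from normal.

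**The concern.** An attrition allowance exists so that the required number of patients remains after the assumed losses. Here the required number is 63 per group and the assumed loss is 25%, so 75% of the enrolled number should be at least 63. With 78 enrolled it is not. The stated 80% power therefore does not follow from the plan's own attrition assumption.

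At stake is how a null result would be read. Follow-up runs to one year, so losses matter in this design. The Discussion also suggests that the sample size could support firm conclusions. Readers would credit the trial with a type II error of 20% when the plan's own assumptions imply about 23.5%.

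**Working it through.** **Inputs.** From Sample size calculation: n = 63 completers per group, d = 0.5, power 80%, type I error 5%, attrition 25%, 78 enrolled per group. From Methods and study design: 1:1 allocation. From Statistical analysis: two-sample Student's t. Assumed: a two-sided test, and no outcome information from patients lost to follow-up.

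**1. Reproduce the 63.** The normal approximation is n = 2(z₀.₉₇₅ + z₀.₈₀)² / d² = 2(1.960 + 0.842)² / 0.25 = 62.8, which rounds up to 63. A one-sided 5% test would need only 50 (51 by the exact t-test), so two-sided is the only reading that fits. The exact two-sided t-test needs 63.77, so 64. The printed 63 is thus the normal-approximation figure, one patient short of the exact one.

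**2. Reproduce the 78.**

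| Route | Result per group | Gives 78? |
|---|---|---|
| 63 / (1 − 0.25) | 84 | No |
| 63 × (1 + 0.25) | 78.75 | Only if truncated |
| 63 / (1 − 0.20) | 78.75 | Only if truncated, and the rate is not the printed 25% |
| 64 / (1 − 0.25) | 85.3, so 86 | No |
| 64 × (1 + 0.25) | 80 | No |

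Dividing by the retained fraction, with the printed rate, does not give 78. The gap to 84 is 6 per group, or 12 in total (168 against 156).

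**3. What 78 delivers.** Completers at 25% loss: 78 × 0.75 = 58.5 per group. Largest loss that keeps 63: 1 − 63/78 = 15/78 = 19.2%. Check on the alternative: 84 × 0.75 = 63.

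**4. Power at d = 0.5, two-sided 5%.** The exact values use the noncentral t distribution. The normal approximation is Φ(d√(n/2) − 1.960); for n = 58.5 this is Φ(0.5 × 5.408 − 1.960) = Φ(0.744) = 77.2%.

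| Completers per group | Exact t | Normal approximation |
|---|---|---|
| 58 | 76.1% | 76.8% |
| 58.5 | 76.5% | 77.2% |
| 59 | 76.8% | 77.5% |
| 63 | 79.5% | 80.1% |
| 64 | 80.1% | 80.7% |

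**5. Split of the gap (exact t).** From 80% to 79.5% is about 0.5 point, due to using 63 and not 64. From 79.5% to 76.5% is 3.0 points (3.4 if 58 remain), due to the attrition step.

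**6. Detectable effect.** With 58.5 per group, 80% power is reached at d = 0.522 (0.525 with 58, 0.520 with 59).

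**The case against.** The best case on the other side accepts the arithmetic and disputes its weight. Four points deserve an answer.

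- **Origin of 78.** A reader might infer that the allowance was certainly computed as 63 × 1.25. The article prints no formula, and a 20% rate with the valid formula gives the same 78.75. The slip could lie in the percentage. This stands: the route is probable, not established. The disagreement among 63, 25% and 78 does not depend on it.
- **Attribution and size.** A reader might charge the whole fall from 80% to the attrition step. The 63 already gives 79.5% by the exact test, so that would overstate it slightly. With the normal approximation, which is what reproduces 63, power at 25% loss is about 77%. A range of 76–77% is fair.
- **Timing.** The 25% has no visit attached, while outcomes are measured at week 11, six months and one year. If 25% is the cumulative loss at one year, fewer may be lost by week 11, and with losses up to about 19% the 63 remain. The power figure is therefore conditional on 25% loss at the visit analysed. The condition is the plan's own.
- **Consequence.** The Discussion treats effects above d = 0.8 as the possible starting point for changing care, and at 58 per group power for d = 0.8 is about 99%. The shortfall would matter little for effects of that size. The sample size was nevertheless justified at d = 0.5, and it is that claim which is misstated.

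A reader might also infer that adjusting for baseline would recover the lost power. The gain depends on the correlation between baseline and follow-up values, which the article does not give, so the documents do not support that conclusion.

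**Conclusion.** The point holds as an inconsistency among printed figures. With 25% attrition, 78 enrolled per group leaves about 58, not 63, and power for d = 0.5 is about 76% (76–77% across formulas and rounding) against the stated 80%. The enrolment that would keep 63 is 84 per group.

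This rests on two assumptions: a two-sided 5% t-test, which is the only sidedness that reproduces 63, and no outcome data from dropouts, which fits the simple two-group tests in Statistical analysis. The shortfall is modest. The type I error rate is unaffected and the treatment estimate is not biased by it. What is wrong is the stated power under the plan's own assumption.

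**What to change.** Correct the attrition sentence in Sample size calculation in one of two ways:

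- state that 78 per group with 25% attrition leaves about 58 per group and gives about 76% power for d = 0.5 (80% for d = 0.52); or
- state that 78 per group keeps 63 completers only if attrition is at most about 19%.

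In the same sentence, say that the test is two-sided and which visit the attrition rate refers to. Either wording costs one sentence and, with the first, a slightly less favourable stated power. Neither needs extra patients. If the claim of 63 completers after 25% attrition is to be kept instead, the enrolment figure must read 84 per group, 6 more per group than printed.

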### Interventions

#### A brief descrption of trial's arms are shown in Table 1. The intervention of the experimental group

Patients assigned to the experimental group will perform a PNE program consisting of six sessions (10 h) and 18 sessions of therapeutic PE to be performed in six weeks (18 h), with a frequency of three sessions per week. The program will be carried out according to the order shown in Fig. 1.

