### Outcomes variables

All variables will be measured before the intervention, after the intervention (week 11), at six months, and a year. Flowchart of the study can be seen in Fig. 3.

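### The two-sample tests named for SF-36 change, with 25% attrition expected, ignore the earlier scores of patients who leave; a baseline-adjusted repeated-measures model would use them and remove the resulting bias under missing at random

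*Protocol article*

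**What the plan says.** - **Method.** The Statistical analysis section begins its between-group methods with "In order to test the equality of means for numerical variables, we will apply the" Student's t, and gives Wilcoxon–Mann–Whitney as the fallback for clearly non-normal data. Its logistic models predict success or failure, with data-driven variable selection. They do not estimate a treatment difference in mean SF-36.
- **Visits.** Under Outcomes variables: "All variables will be measured before the intervention, after the intervention (week 11), at six months, and a year". The Main outcomes variables section makes the primary outcome the between-group difference in quality-of-life changes at those times.
- **Attrition.** The Sample size calculation section starts from "A total of 63 individuals by each group of treatment" and adds an allowance: "By taking into account an attrition rate of 25"%. This is one figure, not split by arm or visit, and it leads to 78 per group.
- **Burden.** The experimental arm receives a "PNE program consisting of six sessions (10 h) and 18 sessions of therapeutic PE to be performed in six weeks (18 h"), that is 24 sessions and 28 hours. The Control group intervention section gives 15 sessions of thermotherapy and electrotherapy with exercise guidelines, and states no hours.

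**The concern.** Adding patients to cover attrition protects precision. It does nothing about bias if those who stay differ from those who leave, and differ in another way in each arm. A two-sample test of one-year change has no place for the week-11 and six-month scores of a patient who is missing at one year, although the trial will have collected them and they may show why the patient left.

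The arms ask different things of patients. The Interventions section also warns that pain may rise in the first exercise sessions. Loss related to a poor early response, mainly in the experimental arm, is therefore a reasonable risk to plan for. What is at stake is the primary treatment contrast at the later visits.

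**Working it through.** **1. The plan's own figure.** Inputs: "in a magnitude corresponding to 50% of the standard deviation (an effect size of 50"%), "with a probability of 80"%, and "keeping the type I error at a 5% level" (two-sided assumed). Per-group n = 2(1.960 + 0.842)²/0.5² = 62.8, so 63 reproduces. 63 × 1.25 = 78.75, which gives 78 when rounded down; 25% loss from 78 leaves 58.5. That shortfall against 63 is a separate matter and is not used below.

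**2. Assumptions for the illustration (mine, not the documents').** SF-36 score with SD 1 at baseline (B), week 11 (W) and one year (Y). Correlations are 0.6 (B,W), 0.5 (B,Y) and 0.7 (W,Y). There is no true effect, and 25% of each arm is missing at one year. Control loss is random. Experimental loss has probability 1/(1 + exp(−(a − s·x))), where x is the driver of dropout and a is set to give 25%. The SD of one-year change is √(2 − 2 × 0.5) = 1, so all figures compare directly with 0.5 SD.

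**3. Loss follows the week-11 score (x = W, s = 1.2).** Numerical integration gives a mean W of 0.24 among retained experimental patients. By linear regression on W:
- one-year score: 0.7 × 0.24 = 0.17
- baseline: 0.6 × 0.24 = 0.145
- change: (0.7 − 0.6) × 0.24 = 0.024

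Retained patients also had better baselines, so most of the raw-score bias cancels in change. Simulation agrees: 0.17 to 0.18 SD for the raw score and 0.02 to 0.03 SD for change. Swapping the first two correlations gives (0.7 − 0.5) × 0.24 = 0.05 for change.

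**4. Loss follows week-11 change (x = D = W − B).** Var(D) = 2 − 2 × 0.6 = 0.8, so SD(D) = 0.894. Cov(Y − B, D) = 0.7 − 0.5 − 0.6 + 1 = 0.6, so the regression slope is 0.6/0.8 = 0.75.
- s = 1.2 per score SD: mean D among the retained = 0.224 × 0.894 = 0.20; bias = 0.75 × 0.20 = **0.15 SD**
- s = 0.6: mean D = 0.127 × 0.894 = 0.114; bias = 0.75 × 0.114 = **0.085 SD** (0.084 with the first two correlations swapped)

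These are 0.085/0.5 = 17% to 0.15/0.5 = 30% of the target difference. If s is instead expressed per SD of change, which is slightly stronger, 4,000 simulated trials of 78 per arm gave 0.17 and 0.10 SD. The nominal 5% type I error rose to about 16% and 8.5%.

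**5. Using the week-11 data.** An estimate that conditions on B and W had bias of about 0.00 in every scenario of steps 3 and 4. This is expected, because loss there depends only on observed data.

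**6. Other mechanisms.** Large-sample simulation with a true effect of 0.50, correlations of 0.5 to 0.7 (exchangeable or AR(1)), and outcome-related loss driven by deviation from the arm's own mean:

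| Loss, experimental / control | Change from baseline, patients seen at one year | Likelihood estimate using earlier visits |
|---|---|---|
| Unrelated to outcome, any split | about 0.50 | about 0.50 |
| 25% / 25%, same mechanism | about 0.50 | about 0.50 |
| 35% / 15%, follows week-11 score | 0.46–0.50 | 0.50 |
| 35% / 15%, follows unseen one-year score | 0.54–0.64 | 0.57–0.63 |

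The last row is missing not at random. The model leaves 0.07 to 0.13 SD there, with no consistent gain over the change-score test.

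**The case against.** The strongest reply is that the bias is conditional, and that the plan says less than a reader might infer from it. Several stronger readings are not supported.

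- **That the plan tests each visit separately and drops anyone who misses it.** This is the natural reading of the sections together, but it is not stated. Imputation rules or analysis sets may be in a full protocol or SAP that is not shown, and their absence here is no finding. The point rests on the method that is named.
- **That the bias is 0.18 SD, about 35% of the target difference.** This applies to raw one-year scores. The protocol's outcome is change, for which the same scenario gives about 0.02 to 0.03 SD.
- **That loss is expected to differ between arms.** The article gives one rate. Control hours are not stated, the control arm also includes exercise, and the Discussion cites better adherence with group work, which points the other way.
- **That the benefit is bound to be overstated.** With 35% against 15% loss following the week-11 score, the change-score estimate was at or below the true value.
- **That a repeated-measures model removes the bias outright.** It does so only under missing at random with an adequate model.

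All five limits stand. What survives is that the named tests make no use of earlier post-baseline scores and do not adjust for baseline, and a standard alternative does both with data already planned.

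**Conclusion.** The point holds in a conditional form. For a primary outcome measured at three post-baseline visits with 25% attrition expected, two-sample tests are a weaker choice than a baseline-adjusted repeated-measures model. Under the stated assumptions, the bias in one-year change runs from about 0.02 to 0.03 SD (loss follows the week-11 score) to about 0.08 to 0.15 SD (loss follows week-11 change). It is nil when loss is unrelated to outcome or has the same rate and mechanism in both arms.

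The correlations, the dropout model and the difference in mechanism between arms are assumptions; the documents establish none of them. The change should be made because it is cheap and protects against a plausible risk, not because a bias of known size or direction has been shown. Confidence is medium.

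**What to change.** For the primary outcome, replace the two-sample tests in the Statistical analysis section (and in the SAP) with a mixed model for repeated measures:

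- all randomised patients in their assigned arm, and all post-baseline visits;
- arm × visit, baseline × visit and centre as fixed effects, with unstructured covariance;
- the treatment contrast at each stated visit taken from this model. With baseline as covariate, the contrast is the same for score and for change.

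Add one sensitivity analysis that imputes missing experimental-arm outcomes at control-arm levels, because the model's protection holds only under missing at random. Keep the t-test as supportive.

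The cost is SAP wording, modest programming in R (already the chosen software) and reliance on the missing-at-random assumption. No new data are needed.

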### Statistical analysis

Numerical variables will be summarised with means and standard deviations and categorical ones with percentages. Those numerical variables showing a distribution very far from the normal one will be transformed for getting resulting distributions close to the normal one, or in the opposite case, they will be summarised by using percentiles. For the graphical representation of the numerical variables’ distribution in each treatment group, we will use box and whisker plots. For representing categorical variables, pie charts will be used. In order to test the equality of means for numerical variables, we will apply the Student’s t, if the corresponding distributions are not far from the normal one. In the opposite scenario, we will calculate the Wilcoxon–Mann–Whitney statistics. For testing the association between qualitative variables, we will use Chi-squared statistics, if it is allowed by the observed frequencies in the associated joint distribution. On the contrary, we will re-categorise these variables for reducing them to dichotomous ones, if necessary, and will apply the Fisher exact test. As a function of the observed response to the treatment in numerical variables or the observed change in them, we will build several definitions of success/failure for the result of treatment in individuals. We will fit logistic regression models for predicting the success of the treatment by using the previously mentioned definitions. In these models, those variables which show a statistically significant relationship with the corresponding response variables in the univariate analysis and the variable selection procedures will be included. These models will provide us, as a by-product, odds ratio values for estimating the comparative risk of success associated with each explanatory variable corrected by the presence of the other variables included in them. We will obtain estimates for the sensitivity/specificity of predictive rules derived from these models. It will be considered as statistically significant *p*-values lower than 0.05. Data analysis will be carried by using the R statistical software.

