#### Main outcomes variables

The primary outcome measure will be the difference between groups in health-related quality of life changes at different times. The Spanish version of the health Survey SF-36 V2 will be used [61, 62]. SF-36 is a 36-item scale built to assess health status and quality of life. It produces a profile of eight levels of functional health and wellness scores, as well as a summary of psychometric-based mental and physical health. Each scale transforms directly into a scale of 0–100. Higher scores indicate a better quality of life in general.

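### Numerical outcomes are compared by a t-test or a data-chosen rank test with no baseline covariate; a pre-fixed ANCOVA would use the collected baseline more efficiently and keep one estimand

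*Protocol article*

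**What the plan says.** The Statistical analysis section sets one rule for all numerical variables: "In order to test the equality of means for numerical variables, we will apply the" Student's t if the distributions are not far from normal. Otherwise, "In the opposite scenario, we will calculate the Wilcoxon–Mann–Whitney statistics". It does not say how far is too far, or how that will be judged. No covariate enters this comparison. The only multivariable models in the section are logistic models for success or failure of treatment. Their success definitions are built from the observed response and their covariates are picked by significance, so they do not adjust the comparison of means.

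Under Main outcomes variables, the primary outcome is "the difference between groups in health-related quality of life changes at different times", measured with the SF-36. Under Outcomes variables, "All variables will be measured before the intervention", and again at week 11, six months and one year.

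The Sample size calculation asks for "A total of 63 individuals by each group of treatment" to detect half a standard deviation with 80% power, "keeping the type I error at a 5% level", and raises this to 78 per group for 25% attrition. It does not say whether the standard deviation is that of the follow-up score or of the change.

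**The concern.** There are two weaknesses, and both lie in what the text fixes, not in detail it leaves out.

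**Use of baseline.** If the t-test is applied to changes, as the primary outcome definition implies, baseline is used with its slope forced to 1. If it is applied to follow-up scores, baseline is not used at all. Regressing the follow-up score on arm and baseline estimates the slope from the data and is more precise than either for any r strictly between 0 and 1. It also corrects chance baseline imbalance by the right amount, whereas a change score over-corrects when the slope is below 1.

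**Choice of test.** A t-test targets a difference in means; a Wilcoxon-Mann-Whitney test targets a rank-based quantity. If the observed distribution decides between them for each variable, without a stated threshold, the estimand can differ from outcome to outcome and is not known in advance. The protocol's Discussion judges the results by Cohen's d, a mean-based measure that a rank test does not supply.

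At stake are power in a trial with little to spare after attrition, and a treatment effect that can be read on the same scale for each outcome.

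**Working it through.** **Inputs from the protocol.** Alpha 0.05; power 80%; standardised difference d = 0.5; 63 per group before attrition; 78 per group recruited; attrition 25%; allocation 1:1. The test is taken as two-sided: sidedness is not stated, but two-sided reproduces 63, while one-sided would need about 51.

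**Assumed input.** The correlation r between baseline and follow-up is not given. I use 0.3 to 0.7, with equal variances s² at the two times.

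**1. Reproduce the plan's figure.** n = 2(1.960 + 0.842)² / 0.5² = 62.8, so 63 per group. The noncentral t gives 64, with power 79.5% at 63. The stated figure is reproduced.

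**2. Patients left to analyse.** 78 × 0.75 = 58.5 per arm. Noncentral-t power for d = 0.5 at 58.5 per arm is 76.5%.

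**3. Variances per patient.**
- Follow-up score: s²
- Change score: 2(1 − r)s²
- ANCOVA: (1 − r²)s²

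The ANCOVA-to-change ratio is (1 − r²) / [2(1 − r)] = (1 + r)/2, a cut of (1 − r)/2. The ANCOVA-to-follow-up ratio is 1 − r², a cut of r².

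| Assumed r | Cut against change score | Cut against follow-up score |
|---|---|---|
| 0.3 | 35% | 9% |
| 0.5 | 25% | 25% |
| 0.7 | 15% | 49% |

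**4. Power at 58.5 per arm** (noncentral t, one degree of freedom deducted for the covariate). The scale of the 0.5 is not stated, so both readings are shown.

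*If 0.5 is in SDs of change*, the change-score test has d = 0.5 and ANCOVA has effective d = 0.5/√((1 + r)/2).

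| Assumed r | Change-score t-test | ANCOVA effective d | ANCOVA power |
|---|---|---|---|
| 0.3 | 76.5% | 0.620 | 91% |
| 0.5 | 76.5% | 0.577 | 87% |
| 0.7 | 76.5% | 0.542 | 83% |

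*If 0.5 is in SDs of the follow-up score*, the follow-up t-test has d = 0.5 (power 76.5%), the change-score test has d = 0.5/√(2(1 − r)), and ANCOVA has d = 0.5/√(1 − r²).

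| Assumed r | Change-score t-test | ANCOVA effective d | ANCOVA power |
|---|---|---|---|
| 0.3 | 62% | 0.524 | 80% |
| 0.5 | 76% | 0.577 | 87% |
| 0.7 | 93% | 0.700 | 96% |

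At r = 0.5 the change and follow-up variances are equal, so the two readings coincide.

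**5. Cost of adding health centre.** Ten centres use nine more degrees of freedom. Deducting these as well changes power by less than 0.1 percentage point in every case above. This counts the degrees of freedom only and assumes no gain from centre differences.

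**The case against.** A reader might infer that the plan ignores baseline altogether. It does not support that: the primary outcome is defined as a change, so baseline enters by subtraction. A reader might also infer that the planned test is biased or invalid. It is neither; under randomisation, a t-test on changes or on follow-up scores is unbiased on average and keeps its type I error.

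The size of the gain rests on r, which the documents do not give, and it varies a good deal. On the follow-up-SD scale at r = 0.3, ANCOVA only just reaches 80%. At r = 0.7 it adds about 3 points to a change-score test that already has 93%. No single percentage should be quoted without its r and its comparator.

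Not every outcome can be handled this way, despite the statement that all variables are measured beforehand. Satisfaction with the treatment received (CSQ-8) cannot exist before treatment, and health-service visits are described as registered during follow-up.

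On the switch of test, transformation appears in the sentence about summarising variables, so the stated test rule has two branches, not three. Nothing shows that the SF-36 would trigger the rank test. That it could end without a mean difference is a possibility the rule leaves open, not a prediction.

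Finally, an unseen analysis plan might specify covariates. But the protocol does not leave the method open: it names the tests. All these limits stand, and none removes the point.

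**Conclusion.** The point holds as one of precision and of a consistent estimand. The protocol fixes a less efficient comparison than its own data allow, and lets the observed distribution choose between tests of different quantities without a stated criterion.

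Under an assumed r of 0.3 to 0.7 and equal variances at baseline and follow-up, ANCOVA is more precise than both possible t-tests, and in every case computed it reaches at least 80% power with the 58.5 per arm expected after attrition. The planned t-test has 76.5% when 0.5 SD is on the scale of the score being tested. If the 0.5 is in SDs of the follow-up score, the change-score test ranges from 62% to 93%. Below r = 0.5 the change score is noisier than the follow-up score alone, so subtraction then costs precision.

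This is a worthwhile improvement to the plan, not an error that would invalidate the trial.

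**What to change.** For the SF-36 and each numerical secondary outcome with a true baseline, replace the choice between t-test and rank test by one pre-specified linear model at each follow-up time (week 11, six months, one year): follow-up score on arm and baseline score of the same outcome, optionally with health centre. Report the adjusted mean difference with its 95% confidence interval. If an outcome is skewed, keep the model and use robust or bootstrap intervals. Keep the Wilcoxon-Mann-Whitney test as a sensitivity analysis only.

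Leave CSQ-8 out of the baseline-adjusted model, and include health-service visits only if a count before the intervention is collected.

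The cost is one degree of freedom for baseline, nine more if the ten centres are included (negligible loss of power), and wording in the analysis plan. For these outcomes the protocol already schedules the baseline measurement.
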